### **7.2 Methods and Timing for Assessing, Recording, and Analyzing Safety Parameters**

Annual reports of our safety measures will be delivered to our Data Safety Monitoring Board.

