## **5. STUDY INTERVENTIONS**

### **5.1 Interventions, Administration, and Duration**

The intervention period will be 18-months in length for all participants, with a one year follow-up period to measure persistence of effects after interventions end. The pre-intervention baseline period will be 6 months in length.

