### 6.2.2 Enrollment, Baseline, and/or Randomization

#### Enrollment

Enrollment date will be documented on the online consent form at the time of consent. Interventions will be initiated after all clinicians in a practice have been enrolled or declined to participate.

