### **7.4 Reporting Procedures**

The Principal Investigator will report any unanticipated events to the IRB as well as the Data Safety and Monitoring Board (DSMB) assembled for this study. When notified of an unanticipated event, the DSMB will convene and make a decision as to whether the study should continue. The IRB will also be notified of the DSMB's decision.

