### **7.5 Safety Monitoring**

A Data Safety and Monitoring Board (DSMB) has been established. The board is composed of three physician experts in acute respiratory infection care, and will meet biannually throughout the duration of the study to review patient safety and adverse events. This board is composed of 3 members both within and outside the University: 1) [name], Assistant Dean for Research Integrity; Co-Director, Division of Biostatistics; Professor of Preventive Medicine, USC Keck School of Medicine, 2) [name], MHS, Associate Professor, Division of General Internal Medicine Director, Duke Primary Care Research Consortium Associate Director, Duke Evidence-based Practice Center, Duke Clinical Research Institute and 3) [name]

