## **8. INTERVENTION DISCONTINUATION**

Following each DSMB meeting, the board will make recommendations to the local IRBs as to whether the study should continue or if changes to the protocol are necessary for continuation.

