### **9.3 Interim analyses and Stopping Rules**

No interim analysis will be conducted on primary or secondary outcomes. The Data Safety and Monitoring board is granted the power to recommend discontinuation of the study to each study IRB, if safety concerns are found. The board will meet biannually throughout the duration of the study to review patient safety and adverse events. Following each meeting, the board will make recommendations to the local IRBs as to whether the study should continue or if changes to the protocol are needed. Data for patients who have a return visit to a study clinic within 30 days of an eligible study visit with a diagnosis that could represent a serious complication of an untreated bacterial infection (e.g. acute rheumatic fever, head and neck abscess, intracranial abscess, Lemierre syndrome, mastoiditis, meningitis, pneumonia, sepsis, etc.) will be extracted from study site EHRs and reported to the Board.

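### Safety reports reach the board once a year, but the board meets twice a year and makes a recommendation each time, so about every second meeting has no new scheduled report

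*Protocol*

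**What the plan says.** Section 7.2, whose heading covers the timing of safety assessment, consists of one sentence: "Annual reports of our safety measures will be delivered to our Data Safety Monitoring Board". No other section sets a frequency for safety reports, and none says when the annual clock starts.

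Section 7.5 says that the board "will meet biannually throughout the duration of the study to review patient safety and adverse events", and Section 9.3 repeats this. Section 8 ties an action to each meeting: "Following each DSMB meeting, the board will make recommendations to the local IRBs as to whether the study should continue", or whether the protocol needs changing. Sections 9.3 and 11.4 say the same.

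Section 7.3 defines adverse events as the count and rate of 30-day return visits with one of the listed diagnoses. These are the measures computed under Section 7.1, which adds chart review of a random 20% of those return visits.

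On duration, Section 5.1 states: "The intervention period will be 18-months in length for all participants, with a one year follow-up period to measure persistence of effects after interventions end". On the start, Section 6.2.2 states: "Interventions will be initiated after all clinicians in a practice have been enrolled or declined to participate".

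Two other routes lead to the board. Sections 7 and 9.3 say that data on return visits with possible serious complications are extracted and reported to it, without a frequency. Section 7.4 says: "The Principal Investigator will report any unanticipated events to the IRB as well as the Data Safety and Monitoring Board". The board then convenes outside its schedule.

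**The concern.** The board is asked to review a quantity twice a year that the timing section sends it once a year. A board that meets without new figures can only repeat its last recommendation or make one without evidence.

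This matters more here than in many quality-improvement trials. The interventions aim to reduce antibiotic prescribing, and the harm that the protocol itself names is complication of untreated bacterial infection. Section 9.3 plans no interim analysis of the outcomes and gives the board the power to recommend discontinuation on safety grounds. Section 6.1 has adverse events monitored continuously up to the end of the intervention and not in the follow-up period. A 12-month reporting interval is long against an 18-month intervention, and a report that arrives after month 18 describes interventions that have already ended.

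**Working it through.** The protocol states no number of safety reports, so there is no figure of its own to reproduce. The check counts scheduled dates.

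**Inputs**
- Report interval: 12 months (7.2).
- Meeting interval: 6 months (7.5, 9.3), reading the term as twice a year, its ordinary meaning. Reading it as every two years would not remove the mismatch.
- Intervention: months 0 to 18 (5.1).
- Month of the first report after the intervention starts, *s*: not stated. It is treated as an assumption and varied over 0 < *s* ≤ 12.

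**Step 1: annual reports before month 18.** Count the dates *s*, *s* + 12, … that fall before 18. There are two if *s* + 12 < 18, that is, if *s* < 6, and otherwise one.

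| First report (month) | Reports before month 18 | Next report |
|---|---|---|
| 3 | 3 and 15 | 27 |
| 5 | 5 and 17 | 29 |
| 6 | 6 | 18, as the intervention ends |
| 9 | 9 | 21 |
| 12 (clock starts with the intervention) | 12 | 24 |

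So the count is one or two, and it is two for half of the possible start dates (6 of 12 months). If the clock starts with the intervention, the only report comes after 12/18 = 67% of the intervention.

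**Step 2: staggered starts.** Practices may start at different times (6.2.2), so the calendar window may exceed 18 months. By how much is not stated. As illustrations only, a 21-month window still gives one or two annual reports, and a 24.5-month window gives two or three.

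**Step 3: meetings against reports.** A report is new to one meeting only, the first that follows it. Any 12 months hold two meetings (12/6 = 2) and one report (12/12 = 1), so one meeting in two has no new report. This does not depend on *s*.

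Within the common 18-month intervention:
- Meetings at months 6 and 12: the periods they cover, 0–6 and 6–12, together hold one report, so one of the two meetings has none.
- Three meetings, for example months 3, 9 and 15: the periods they cover span 18 months and hold one or two reports, so one or two of the three meetings have none.

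At least one meeting during the intervention therefore has no new scheduled report.

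**Step 4: the same count with six-monthly reports.** If the clock starts with the intervention, reports fall at months 6 and 12, with a third at month 18 as it ends. The first then comes at 6/18 = 33% of the intervention. With any other start date, three fall before month 18. Each meeting then has a new report.

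**The case against.** The best defence is that the annual report is not the board's only source. Sections 7 and 9.3 say that return-visit data are reported to the board and set no annual limit. In Section 9.3 that sentence belongs to the same paragraph as the twice-yearly meetings. One can read the plan as six-monthly review of adverse-event counts, with a compiled report, perhaps including the chart review, once a year. Section 7.4 adds an unscheduled meeting.

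Part of this stands: the board is not confined to the annual report. But the reading has to be supplied by the reader. Neither Section 7 nor Section 9.3 says when the return-visit data are delivered, and the section that does address timing says annual. Section 7.4 is limited to unanticipated events, while meningitis, sepsis, abscess and similar complications are named in advance in Section 7. The protocol does not say whether such a case counts as unanticipated.

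Several stronger readings are tempting and are not supported:
- That at most one report can arrive during the intervention. This needs the annual clock to start with the intervention and all practices to start together, and the protocol fixes neither.
- That the board cannot react in the first year, or that a signal after month 12 cannot affect the intervention. The return-visit data, the Section 7.4 meeting and a possible second report all leave room for action.
- That the board alone can act on harm. It recommends to the local IRBs, and unanticipated events go to the IRB as well.
- That some 50,760 visits pass before the first report (282 providers × 15 visits × 12 months, from Section 9.2). This takes every provider as full time, includes control practices, and assumes that the clock starts with the intervention. It is an upper bound on visits, not a count of patients put at risk by late reporting.
- That every case in which earlier antibiotics might have helped must go to the board at once. That would be a new reporting rule, not the repair of a contradiction.

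**Conclusion.** The mismatch is real and does not depend on the start of the clock: annual safety reports serve a board that meets and recommends every six months, so about every second meeting has no new scheduled report. During the intervention this affects at least one meeting. The number of annual reports before month 18 is one if the clock starts with the intervention, and one or two over all start dates, for a common 18-month window. The result rests on twice-yearly meetings and on Section 7.2 being the operative statement of timing. The other two routes soften the consequence but do not clearly close the gap. The point should be corrected, because it concerns whether the protocol's safety review can work as described. It does not show that the board would be without safety information.

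A separate inconsistency lies in the same text: under Section 7.4 the board makes a decision on continuation, while under Sections 8, 9.3 and 11.4 it makes recommendations to the IRBs.

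**What to change.** In Section 7.2, replace the annual reports with a safety report delivered before each twice-yearly board meeting during the intervention. State its content: the Section 7.1 counts and rates of return visits with a listed diagnosis, and the chart-review classifications available to date. Have Sections 7 and 9.3 refer to this report, so that the return-visit data have a stated frequency.

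Separately, reconcile Section 7.4 with Sections 8, 9.3 and 11.4 on whether the board decides or recommends. State also whether the complications listed in Section 7 count as unanticipated under Section 7.4.

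The cost is small. Records already reach the coordinating center weekly (Sections 3 and 10.2) and the meetings are already planned. What is added is one or two extra runs of an existing extract, and chart review of the same 20% sample on an earlier schedule. The design, sample size and primary analysis are unaffected.

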### **7.3 Adverse Events**

Adverse events are defined as the number of return visits occurring within 30 days of index visits (and associated rate of return) with a diagnosis of concern (See Appendix E for diagnoses of concern at revisit).

### **7.4 Reporting Procedures**

The Principal Investigator will report any unanticipated events to the IRB as well as the Data Safety and Monitoring Board (DSMB) assembled for this study. When notified of an unanticipated event, the DSMB will convene and make a decision as to whether the study should continue. The IRB will also be notified of the DSMB's decision.

### **7.5 Safety Monitoring**

A Data Safety and Monitoring Board (DSMB) has been established. The board is composed of three physician experts in acute respiratory infection care, and will meet biannually throughout the duration of the study to review patient safety and adverse events. This board is composed of 3 members both within and outside the University: 1) [name], Assistant Dean for Research Integrity; Co-Director, Division of Biostatistics; Professor of Preventive Medicine, USC Keck School of Medicine, 2) [name], MHS, Associate Professor, Division of General Internal Medicine Director, Duke Primary Care Research Consortium Associate Director, Duke Evidence-based Practice Center, Duke Clinical Research Institute and 3) [name]

## **8. INTERVENTION DISCONTINUATION**

Following each DSMB meeting, the board will make recommendations to the local IRBs as to whether the study should continue or if changes to the protocol are necessary for continuation.

## **9. STATISTICAL CONSIDERATIONS**

### **9.1 General Design Issues**

#### *Hypotheses*

Our primary hypothesis is that practices randomized to receive behavioral economic interventions will have decreases over time in antibiotic prescribing rates for non-antibiotic appropriate ARIs, compared to contemporaneous antibiotic prescribing rates for non-antibiotic appropriate ARIs among control practices. This hypothesis will be evaluated in an intent-to-treat difference-in-differences framework using a mixed-effects logistic regression model. Fixed effects will include the effects of interventions over time (i.e., interactions between randomization assignment and time), using a 6-months prior to the intervention baseline period. Providers and randomization unit (clinic) will be modeled as random effects.

#### *Design*

We will conduct a between-group factorial cluster randomized trial of ambulatory clinic visits in a national sample of clinics. Clustering (by clinic) helps us prevent treatment contamination between individual clinicians within the same clinic. The factorial design will allow us to study the effects of multiple antibiotic policies as often happens in the real-world, where State and Federal public health as well as clinic organization quality improvement interventions may be happening at the same time. Using this factorial design, three interventions will be tested for their ability to alter inappropriate physician prescribing behavior: 1) Accountable Justifications triggers by guideline-discordant prescriptions that ask providers to provide their rationale for prescribing an antibiotic and include these rationales in the medical record; 2) Suggested Alternatives presents in EHR order sets containing guideline concordant treatment options for ARIs; and 3) Peer Comparisons communicates through emailed performance feedback reports that compare each provider's own performance to his or her top-performing peers.

#### *Outcome measures*

The primary outcome measure is the rate of antibiotic prescribing for non-antibiotic-appropriate acute respiratory infections.

The ICD-9 codes for primary outcomes are defined in detail in Sections 9.4.1 and 9.4.2 of

this protocol document. These outcomes are computable clinical quality measures from the electronic health record. These are widely used in medicine to evaluate quality improvement and reliability and validity are generally supported. As a secondary outcome, effects on potentially appropriate acute respiratory infection diagnosis will be evaluated with respect to diagnostic drift and safety (see Section 9.4.2).

An office visit is eligible for inclusion in the outcome denominator if: 1) the patient was 18 years old or older, 2) the provider and practice site were enrolled in the study, 3) the visit occurred during the 18-month intervention period, and 4) the patient did not have a visit with any ARI diagnosis in the prior 30 days. Visits are excluded from the primary analysis when: 1) patients have certain medical co-morbidities that make ARI guidelines less likely to apply, 2) patients had concomitant visit diagnoses indicating a non-ARI possible bacterial infection, or 3) patients had concomitant visit diagnoses indicating potentially antibiotic appropriate ARI diagnoses or other ARI diagnoses suggestive of a bacterial infection. Visits for which a provider recorded another condition that was not an ARI for which antibiotics might be indicated were also excluded from the analysis.

## 9.2 Sample Size and Randomization

Using the correction for inter-cluster correlation from Kish, we estimated the power of our study to detect a clinically significant difference between binary conditions. That is, the sample size must be inflated by a factor of  $1 + \theta(m-1)$ , where  $\theta$  is the inter class correlation and  $m$  is the number of ARI observations per cluster. In our calculations we assumed an intra-clinic correlation of 0.05 and assumed a baseline antibiotic prescribing rate of 50%, an ARI visit rate of 15 visits per month for full time providers, and independence of treatments in the factorial design. We calculated the number of visits needed for an 80% chance (1 – Type II error) to detect a clinically meaningful difference in antibiotic prescribing (7%). We assumed Type I alpha is equal to 0.05, a 75% recruitment success rate for recruiting 376 eligible providers across 49 sites, resulting in 141 providers per study factor (282 clinicians total) and a one-sided  $\alpha$  of 0.05. To achieve statistical power of 0.80 would require a total of 2,252 visits at each factor level, or 4,504 visits across all study conditions. Therefore, if each provider had a minimum of 16 antibiotic-inappropriate ARI visits over the course of the study, we would have sufficient power to detect a clinically significant effect. Randomization is described next in Section 9.2.1.

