### 9.5 Data Analyses

We will use the following descriptive statistics to characterize the sample: Means and medians for continuous measures, frequencies for count data, standard deviations and interquartile ranges for variance.

For inferential analysis of our hypotheses, we will employ a mixed-effects hierarchical logistic regression model to estimate the adjusted marginal effect over time of each intervention on the primary outcome using. Fixed effects will include intervention assignment, time period dummy variables (the baseline prescribing rate for each clinician, the intervention and intervention months 0-6, 7-12, and 13-18), and time period interacted with intervention assignment. Providers and randomization unit (clinic) will be included as random effects. To isolate the effect of each individual intervention (Suggested Alternatives, Accountable Justification, or Peer Comparison) on the primary outcome, controlling for any co-occurring interventions under the factorial design.

To assess diagnostic drift, we will use the same analytic model as for the primary outcome, but with the percentage of *all* ARIs that is coded as antibiotic-appropriate in each study arm as the dependent variable (a secondary outcome).

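### Section 9.2 claims 80% power at one-sided 0.05 without giving the cluster size; with 49 clinics and its own ICC the power is about 64%, and at most about 71%

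*Protocol*

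**What the plan says.** Protocol section 9.2 inflates the sample size by the Kish factor 1 + ICC × (m − 1). It defines m as the ARI observations per cluster but gives no value for it. Its inputs are:

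- Correlation: "we assumed an intra-clinic correlation of 0.05".
- Baseline rate: the authors "assumed a baseline antibiotic prescribing rate of 50" per cent.
- Target difference: 7%, taken here as percentage points.
- Error rate: "We assumed Type I alpha is equal to 0.05", and later in the same sentence "resulting in 141 providers per study factor (282 clinicians total) and a one-sided" alpha of 0.05.
- Providers and clinics: 282 providers in 49 clinics.

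The result is: "To achieve statistical power of 0.80 would require a total of 2,252 visits at each factor level, or 4,504 visits across all study conditions". Section 9.2 adds that 16 antibiotic-inappropriate ARI visits per provider would be enough.

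Sections 1.1 and 9.1 state the primary hypothesis as a reduction in prescribing. Section 9.5 says that "we will employ a mixed-effects hierarchical logistic regression model to estimate the adjusted marginal effect over time of each intervention on the primary outcome". No section states a two-sided test.

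**The concern.** The sample size in section 9.2 depends on the ICC, the cluster size and the alpha level. The first is stated. The second is missing. The third is given twice, once without sidedness. A reader therefore cannot rebuild 2,252 from the text or tell which test the 80% refers to.

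This matters because, in a trial with a fixed number of clinics, a larger m adds visits but very little information. If m is taken below its clinic-level value, the design effect is too small and the power too high. Section 9.2 would then assure the sponsor and the monitoring board that 16 visits per provider suffice, when the number of clinics is what limits the trial. A null result for one of the three interventions could be read as evidence against a 7-point effect that the trial had well under an 80% chance of detecting.

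**Working it through.** **Inputs, all from section 9.2.** p1 = 0.50, p2 = 0.43, ICC = 0.05, power 0.80, 2,252 visits per level, 4,504 in total, 49 clinics. I assume the clinics split equally, so 24.5 per level, with equal cluster sizes.

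**Step 1: visits per level before clustering.** n = (z_alpha + 0.842)² × [p1(1 − p1) + p2(1 − p2)] / 0.07², where the bracket is 0.25 + 0.2451 = 0.4951.

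- One-sided 0.05 (z = 1.645): n = 625.
- Two-sided 0.05 (z = 1.960): n = 793.

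A pooled-variance formula gives 627 and 796 and changes nothing below.

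**Step 2: try to reproduce 2,252.** The design effect needed is 2,252/625 = 3.60 one-sided, so m = 1 + 2.60/0.05 = 53. Two-sided it is 2,252/793 = 2.84, so m = 38. Values of m that the text can supply give the following (pooled formula):

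| m | Source | Design effect | Visits per level, one-sided | Visits per level, two-sided |
|---|---|---|---|---|
| 15 | visits per provider per month | 1.70 | 1,066 | 1,353 |
| 16 | visits per provider, 4,504/282 | 1.75 | 1,097 | 1,393 |
| 46.0 | 2,252/49 | 3.25 | 2,036 | 2,585 |
| 91.9 | 4,504/49 | 5.55 | 3,477 | 4,415 |

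None gives 2,252 per level. The row with m = 46 also divides one level's visits by the clinics of both levels, although each clinic sits at only one level of a given factor. The nearest match departs from the printed text: if 2,252 were the total and the provider were the cluster (m = 16), one-sided planning gives 2 × 627 × 1.75 = 2,194, and two-sided gives 2,786. A relative 7% reduction (50% against 46.5%) needs about 2,520 visits per level one-sided before any clustering, so it does not explain the figure.

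**Step 3: power with the clinic as the cluster.**

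- m = 2,252/24.5 = 91.9.
- Design effect = 1 + 0.05 × 90.9 = 5.55.
- Effective n per level = 2,252/5.55 = 406.
- SE of the difference = √(0.4951/406) = 0.0349.
- Expected z at 7 points = 0.07/0.0349 = 2.00.
- Power, one-sided 0.05: Φ(2.00 − 1.645) = 0.64.
- Power, two-sided 0.05: Φ(2.00 − 1.960) = 0.52.

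**Step 4: the ceiling.** As m grows, effective n per level tends to 24.5/0.05 = 490. SE = √(0.4951/490) = 0.0318 and z = 2.20, so power tends to 0.71 one-sided and 0.60 two-sided. The required effective n of 625 or 793 is above 490, so more visits cannot reach 80% under either sidedness.

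**Step 5: detectable difference at 80% power**, with the variance held at the Step 1 value.

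- At 2,252 visits per level: (1.645 + 0.842) × 0.0349 = 8.7 points one-sided, and (1.960 + 0.842) × 0.0349 = 9.8 points two-sided.
- At the ceiling: about 7.9 and 8.9 points.

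**The case against.** The strongest reply is that these figures describe a simple comparison of two proportions in the intervention period. Sections 9.1 and 9.5 plan a difference-in-differences mixed model with a 6-month baseline and random effects for clinic and provider. If clinic rates are stable over time, much of the between-clinic variance cancels and real power could be higher. This stands as a possibility. It does not rescue the printed figure: section 9.2 derives its number from the Kish correction, claims no gain from baseline data, and gives no correlation from which to work one out. On the Step 3 numbers the variance would have to fall by 1 − 406/625 = 35% to reach 80% one-sided, or by 1 − 406/793 = 49% two-sided.

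A second reply is that 2,252 is a minimum, and that 15 ARI visits per provider per month over 18 months would yield far more. The share with antibiotic-inappropriate diagnoses is not given. Even if all counted, m would be 15 × 18 × 282/49 = 1,554 and one-sided power about 70%. The ceiling in Step 4 already covers this.

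A third reply concerns alpha. A reader might infer that section 9.2 states two conflicting levels, or that the silence of section 9.5 on sidedness lets a borderline result be called either way. The text supports neither. Both mentions give 0.05 and the second adds the sidedness. One-sided testing agrees with the directional hypotheses in sections 1.1 and 9.1. The level and sidedness of the model test are commonly left to the SAP, which is not at hand. Preferring two-sided 0.05 is a convention and does not correct an error.

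**Conclusion.** The point holds as one about power. At the level the protocol declares, one-sided 0.05, the 80% claim is not supported by section 9.2's own inputs: power is about 64% at 2,252 visits per level and at most about 71%. If the final test is two-sided at 0.05, the figures are about 52% and about 60%. These results assume 50% against 43%, clinic ICC 0.05, an equal split of 49 clinics, equal cluster sizes, and no gain from baseline adjustment.

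A reader might also infer that 2,252 is incompatible with any alpha. That goes too far. Because m is missing, the figure fits one-sided 0.05 at m of about 53 and two-sided 0.05 at about 38. The mismatch comes from the unstated cluster size and not from alpha. The double mention of alpha is loose wording. Its practical effect is that the stated 80% applies, at best, to a one-sided test: if m were 53, a two-sided 0.05 test on the same visits would have about 70% power.

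**What to change.** In section 9.2, state alpha and its sidedness once, and use the same level for the primary tests and their confidence intervals. If one-sided 0.05 is kept, the matching two-sided interval is 90%. If the final test will be two-sided at 0.05, restate power for that test.

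State the m that was used and whether it counts visits per clinic or per provider. Then give the power for 7 points, or the difference detectable with 80% power, for 49 clinics at the chosen level. The assurance about 16 visits per provider should be revised to match.

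If the sponsor relies on the baseline period to recover power, section 9.2 should say so and give the assumed correlation between baseline and intervention-period clinic rates, so that the gain can be checked.

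The change is a few sentences of protocol text and a recalculation, with no new clinics or data. Its downside is that the stated power becomes less favourable unless a baseline gain can be justified.

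### Section 9.2's own formula and inputs give about 64% power, not 80%, at 4,504 visits (16 per provider)

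*Protocol*

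**What the plan says.** Section 9.2 of the protocol contains its sample-size justification. It applies the Kish inflation factor, with m defined as the ARI observations in each cluster. Its inputs are:

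- ICC and control rate: "In our calculations we assumed an intra-clinic correlation of 0.05 and assumed a baseline antibiotic prescribing rate of 50" per cent.
- A difference of 7%, read here as 7 percentage points (50% versus 43%).
- Power of 80%.
- Recruitment of 75% of 376 eligible providers across 49 sites, "resulting in 141 providers per study factor (282 clinicians total) and a one-sided" alpha of 0.05.
- Independence of the treatments in the factorial design, so each main effect compares about half of the clinics with the other half.

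The result is stated as: "To achieve statistical power of 0.80 would require a total of 2,252 visits at each factor level, or 4,504 visits across all study conditions". From this the section concludes that "if each provider had a minimum of 16 antibiotic-inappropriate ARI visits over the course of the study, we would have sufficient power".

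Sections 6.2.2 and 9.2.1 make the individual clinic the unit of randomization. Sections 9.1 and 9.5 plan a difference-in-differences mixed logistic model with a 6-month baseline and random effects for provider and clinic. Section 9.2 takes no stated credit for the baseline.

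**The concern.** The correlation is called intra-clinic and randomization is by clinic, so the clusters in the inflation formula are the 49 clinics. At about 92 visits per clinic and an ICC of 0.05, the design effect is well above what 2,252 visits per level allows for. With the number of clinics fixed, further visits also raise m and hence the design effect, so the effective sample size levels off.

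What is at stake is the threshold. Section 9.2 tells the reader that 16 antibiotic-inappropriate visits per provider secure 80% power for a 7-point effect. Anyone judging whether enough visits have accrued, or how informative a non-significant main effect is, would be relying on a figure that its own method does not support.

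**Working it through.** **Inputs (all from Section 9.2 unless noted).** Rates 0.50 and 0.43; one-sided alpha 0.05 (z = 1.645); power 0.80 (z = 0.842); ICC 0.05; 49 clinics, so 24.5 per factor level; clinic as cluster (also Section 9.2.1).

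**Figures that reproduce.** 376 × 0.75 = 282 providers; 282 / 2 = 141 per level; 141 × 16 = 2,256, which covers the stated 2,252.

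**Figure that does not reproduce: 2,252 per level.**

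1. Independent visits per level: (1.645 + 0.842)² × (0.50 × 0.50 + 0.43 × 0.57) / 0.07² = about 625. A pooled-variance version gives 627.
2. Visits per clinic: m = 4,504 / 49 = 91.9.
3. Design effect: 1 + 0.05 × 90.9 = 5.55.
4. Visits needed per level at that cluster size: 625 × 5.55 = about 3,465.
5. Back-calculation: 2,252 / 625 = 3.60, so m = 1 + 2.60 / 0.05 = about 53 visits per clinic, and 4,504 / 53 = about 85 clinics. The protocol has 49.

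**Other readings tried.** A two-sided alpha, a continuity correction, rates centred on 50% and 7% as a relative difference do not give 2,252 per level with 49 clinics. The nearest match treats the provider as the cluster: with m = 17 the design effect is 1.80, and 2 × 625 × 1.80 = 2,250. That is a total over both levels, and it uses a provider-level correlation. It may be where the figure came from, but it fits neither the per-level label nor the intra-clinic ICC.

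**Power at the stated visit count.**

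- Effective sample per level: 2,252 / 5.55 = 406.
- Power: Φ(0.07 / √(0.4951 / 406) − 1.645) = Φ(0.36) = 64%.

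**Limit with unlimited visits, no baseline adjustment.**

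- Effective sample per level: 24.5 / 0.05 = 490, below the 625 needed.
- Power: Φ(0.07 / √(0.4951 / 490) − 1.645) = Φ(0.56) = 71%.

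**Detectable difference at 80% power.** Solving d = 2.487 × √((0.25 + (0.5 − d)(0.5 + d)) / n) gives 8.7 points at n = 406 and 7.9 points at n = 490.

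**What baseline adjustment could do.** The protocol gives no between-period clinic correlation r, so this part rests on assumptions: r from 0 to 1, baseline visits one third of intervention visits (6 versus 18 months), variance 0.25 and ICC 0.05 in each period. With m₁ and m₀ the intervention and baseline visits per clinic, V₁ = 0.25 × (0.05 + 0.95/m₁), V₀ is the same with m₀, and C = 0.25 × 0.05 × r. The variance per clinic is V₁ + V₀ − 2C for pure differencing and V₁ − C²/V₀ when the baseline is a covariate. The effect variance is 2/24.5 times that. One-sided power:

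| Intervention visits per clinic | r | Differencing | Baseline covariate |
|---|---|---|---|
| 92 | 0 | 37% | 64% |
| 92 | 0.8 | 63% | 78% |
| 92 | 0.9 | 70% | 83% |
| 92 | 1.0 | 78% | 89% |
| 400 | 0.7 | 79% | 87% |
| 400 | 0.8 | 89% | 93% |
| 1,500 | 0 | 45% | 70% |
| 1,500 | 0.5 | 69% | 80% |
| 1,500 | 0.7 | 86% | 91% |

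For scale, the assumed 15 ARI visits per month over 18 months for 282 providers is 76,140 visits, or about 1,550 per clinic. That is an upper bound, because it takes every provider as full time and every ARI visit as eligible for the primary outcome.

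**The case against.** The best case for the plan is that Section 9.2 is not the analysis. The primary model uses a 6-month baseline, stable differences between clinics then largely cancel, and 16 visits is given as a minimum against an assumed 15 ARI visits a month. On that view the trial may well have 80% power.

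Most of this stands, and it limits the point. A reader might infer from the 71% limit that 80% power is out of reach for this trial with 49 clinics. The documents do not support that: the limit belongs to the unadjusted comparison that Section 9.2 calculates, and the table shows differencing above 80% at several hundred visits per clinic when the clinic correlation is about 0.8. Nor do they support saying that the trial will miss a true 7-point effect about one time in three, since that treats 4,504 visits, unadjusted, as the trial.

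The objection does not rescue the stated figure. Section 9.2 claims no baseline credit and gives no between-period correlation. Under pure differencing, 4,504 intervention visits stay below 80% even at r = 1. Section 9.5 lists each clinician's baseline rate among the fixed effects. Read as covariate adjustment, that passes 80% at this volume only for r between 0.8 and 0.9 or higher. Section 9.5 also specifies period-by-intervention interactions, so that reading is not settled.

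A reader might also want the gap quoted for a two-sided test. Section 9.2 states a one-sided alpha and the hypothesis is directional, so sidedness is a separate question and is left out here.

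**Conclusion.** The point holds for what Section 9.2 states. By its own formula and inputs, 2,252 visits per level (4,504 in total, 16 per provider) give about 64% power, not 80%; about 3,465 per level would be needed at that cluster size; and without baseline adjustment the limit is about 71%.

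This rests on the clinic being the cluster, on 7% being an absolute difference and on an even split of clinics for each factor. It is not sensitive to the choice of formula: a pooled variance gives 64% and 71%, and a t-test on 47 degrees of freedom gives 63% and 70%. It does depend on the ICC. At 4,504 visits the stated 80% would hold if the ICC were about 0.028 or lower, but the protocol fixes 0.05.

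The conclusion is that the sufficiency statement is wrong. Whether the planned analysis reaches 80% is open, because it depends on a between-period clinic correlation and an eligible visit volume per clinic that the protocol does not give.

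**What to change.** Replace the 2,252 / 4,504 / 16-visit statement in Section 9.2 in one of two ways.

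- Report what the formula gives with 49 clinics: about 64% power at 4,504 visits, a limit of about 71% without baseline adjustment, and a detectable difference of about 8.7 points (7.9 at the limit).
- Or recompute for the planned baseline-adjusted model with 49 clinics. State the level at which the ICC applies (clinic or provider), the within-period ICC, a range of between-period clinic correlations and the expected antibiotic-inappropriate ARI visits per clinic, and give the visits per clinic needed for 80%.

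The second is more useful, because it matches the analysis in Sections 9.1 and 9.5. The cost is one rewritten paragraph and a short calculation; the stated power becomes less favourable or is tied to a higher visit count. No clinics need be added, and the stated sidedness need not change for this fix.
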